### Outcomes

Outcomes were selected based on our previously developed Core Outcome Set (COS), established and published by our TCU consortium using a systematic review, the Delphi study, with healthcare professionals and focus groups with parents.^26 27^ A COS is considered a fundamental list of outcomes and is meant to add outcomes relevant to a specific study. Therefore, additional outcomes were selected through discussion within our TCU consortium. A full overview of outcomes including measurement tools and timing is presented in table 1.

**Table 1 T1:** Overview outcomes, measurement tools/parameters and timing of outcomes BRIDGE study

	Outcome	Measurement tool/parameters	Measurement points
Primary outcome	Parental distress	Distress thermometer for parents	JPH/hospital discharge, 3 months and 12 months follow-up
Parent-focused (secondary) outcomes	Parental anxiety	PROMIS V.1.0 – anxiety 4a	JPH/Hospital discharge, 3 months and 12 months follow-up
	Parental depression	PROMIS V.1.0 – depression 4a	JPH/Hospital discharge, 3 months and 12 months follow-up
	Parental sleep disturbance	PROMIS Short Form V.1.0 sleep disturbance 4a	JPH/Hospital discharge, 3 months and 12 months follow-up
	Self-efficacy of parents	Parental measure of self-efficacy managing a child’s medications and treatments	JPH/Hospital discharge, 3 months and 12 months follow-up
	PTSD parents	PTSD checklist for Diagnostic and Statistical Manual of Mental Disorders-5	3 months and 12 months follow-up
	Financial impact	Self-constructed questionnaire (see online supplemental file 6)	12 months follow-up
Family-focused (secondary) outcomes	Impact on the life of the family	The family impact module of the Paediatric Quality of Life Inventory	JPH/hospital discharge, 3 months and 12 months follow-up
	Satisfaction with received care	Measures of processes of care	JPH/hospital discharge
Child-focused (secondary) outcomes	Child's quality of life	Standard set of patient reported outcomes and generic patient reported outcome measures for Dutch children (see online supplemental file 4)	JPH/hospital discharge, 3 months and 12 months follow-up
	Growth	Weight for age, weight for height and height for age	Study inclusion, JPH/hospital discharge, 3 months and 12 months follow-up
	Parent-perceived health status of the child	Self-constructed questionnaire (see online supplemental file 6)	JPH/hospital discharge, 3 months and 12 months follow-up
Health system (secondary) outcomes	Healthcare consumption	Length of hospital/JPH stay, number of (PICU) readmissions, emergency department visits and visits to the general practitioner (GP) or GP emergency services	12 months of follow-up

JPH, Jeroen Pit Huis ; PICU, pediatrics intensive care unit; PTSD, post-traumatic stress disorder.

#### Primary outcome

The primary outcome is parental distress at discharge home and will be measured by the distress thermometer for parents (DT-P).^28^ This includes (1) a thermometer score regarding overall distress in the past week, with a score from 0 (no distress) to 10 (extreme distress), (2) a problem list which inquired the occurrence of 37 (child age <2 years) or 34 (child age≥2 years) everyday problems over the past week across six domains (practical, family/social, emotional, physical, cognitive and parenting), where problem domain scores are the sum of item scores (yes=1, no=0) within that problem domain and (3) additional questions concerning: perceived support from surroundings, perceived lack of understanding from people concerning their situation and parental chronic illness. Internal consistency of the DT-P was in the range of (*α*) = 0.52–0.89.^29^

#### Parent-focused (secondary) outcomes

The measured outcomes for parents will include anxiety, depressive symptoms, sleep disturbance (SD), self-efficacy, post-traumatic stress disorder (PTSD) and financial impact.

The PROMIS V.1.0 – anxiety 4a and the PROMIS V.1.0 – depression 4a short forms will be used to assess symptoms of respectively anxiety and depression in parents.^30^ Both measures comprise 4 items, scored on a 5-point Likert scale ranging from ‘never’ to ‘almost’ using a 7-day recall period. Total raw scores are calculated and transformed into a T-score with a mean of 50 and SD of 10. Higher scores indicate more anxiety or depression symptoms. Psychometric properties of Patient Reported Outcome Measurements (PROMS) are sufficient.^31^

Parental SD will be assessed with the short form 4a PROMIS SD.^32^ The 4-item questionnaire will be used to measure self-reported perceptions of sleep quality, depth and restoration within the past 7 days. This measure comprises a 5-point Likert scale ranging from ‘never’ to ‘almost’ using a 7-day recall period. The raw score will be converted into a T-score with a mean of 50 and SD of 10. Higher scores indicate more sleep/wake disturbances. Psychometric properties of PROMS are sufficient.^31^

Self-efficacy will be measured using the Parental Measure of Self-Efficacy Managing a Child’s Medications and Treatments.^33^ This tool is adapted from the PROMIS self-efficacy patient-reported outcome (PRO) measure that assesses adults’ self-efficacy in managing their own medications and treatments.^34^ The scale consists of 30 items, of which 14 items are relevant to children regardless of condition severity (eg, healthcare information/decision making; symptom identification/management) and 16 items are relevant to children with specific healthcare needs (eg, medication usage, equipment). This measure comprises a 5-point Likert scale ranging from ‘I am not confident at all’ to ‘I am very confident’. Scores will be obtained by summing the mean scores of the 30 items, ranging between 30 and 150, with higher scores indicating higher self-efficacy. The questionnaire, initially available only in English, underwent translation into Dutch using the Functional Assessment of Chronic Illness Therapy translation methodology, a method recommended by the PROMIS Health Organisation.^35 36^ For an overview of the translation process, see online supplemental file 5. No psychometric properties are available yet.

PTSD checklist (PCL) for Diagnostic and Statistical Manual of Mental Disorders (DSM)-5 (PCL-5) will be used to screen for symptoms of PTSD, with a 1-month recall period, based on the DSM-IV criteria. The PCL-5 includes 20 items, scored on a Likert scale ranging from 0 to 4, reflecting the DSM-5 diagnostic criteria of PTSD. A higher sum score represents more pronounced PTSD symptoms, and a cut-off score of 31 was used to screen for PTSD. Four subscales can be calculated: intrusion, avoidance, emotion alterations and hyperarousal.^37^ Internal consistency of the PCL-5 is (*α*) = 0.93.^38^

Financial impact on parents will be measured through a self-conducted survey, developed by the authors in consultation with TCU consortium members, including a parent representative. This survey will assess the financial impact based on the ability to work and changes in the financial situation due to the consequences of the child’s illness (see online supplemental file 6).

#### Family-focused (secondary) outcomes

The assessed outcomes for families will encompass the impact on their overall family life and satisfaction with the care received, emphasising the extent to which these services are family-centred.

The Pediatric Quality of Life Inventory Family Impact Module (PedsQL FIM) will be used to assess family impact in the last 4 weeks.^39^ The PedsQL FIM measures parent self-reported physical, emotional, social and cognitive functioning, communication and worry. Additionally, parent-reported family daily activities and family relationships will be measured. The scale consists of 36 items with a 5-point response scale (0=never a problem; 4=always a problem). The questionnaire yields three summary scores: the parent health-related quality of life summary score (which is calculated by averaging items in the physical, emotional, social and cognitive functioning scales), the family functioning summary score (which is calculated by averaging items in the daily activities and family relationships scales) and the total impact score (which is calculated by averaging items in all eight scales). Internal consistency of the English PedsQL FIM was in the range of (*α*) = 0.82–0.97.^39^ No Dutch psychometric properties are available yet.

Parental perceptions of care will be evaluated using the Measures of Processes of Care (MPOC-20),^40 41^ which measures caregiver perceptions of the extent of family-centredness of the care received by children with disabilities in a healthcare organisation. The MPOC-20 is composed of 20 items covering five scales (1) enabling and partnership; (2) coordinated and comprehensive care; (3) providing specific information about the child; (4) respectful and supportive care; and (5) providing general information. The items are answered on a 7-point Likert scale ranging from 1 (not at all) to 7 (to a very great extent). A higher score reflects a more favourable judgement of the care process. Internal consistency of the MPOC-20 was in the range of (*α*) = 0.78–0.91^42^

#### Child-focused (secondary) outcomes

The assessed outcomes for CMC will encompass the child’s quality of life, the parent-perceived health status of the child and growth.

Overall quality of life scores and physical, social and mental functioning and fatigue and pain symptoms of the child will be measured according to the standard set of PROs and generic PROMS for Dutch children.^43^ Depending on the age of the children, different questionnaires need to be completed proxy or self-reported (online supplemental file 4). Psychometric properties of PROMS are sufficient^44^,^47^

One question, formulated by the research group, aims to assess the parent-perceived health status of the child. Parents are prompted to indicate their child’s current health condition on a scale from 0 to 100, where 100 represents the best health condition imaginable, and 0 represents the worst health condition imaginable (online supplemental file 6).

Data on standard anthropometric measurements (weight and height) will be collected (if present) at study inclusion, on discharge from the hospital/JPH and 3 months and 12 months after discharge. This data will be extracted from the electronic health record. Interpretation of weight and height will be performed by means of calculating z-scores according to age: weight for age for children <1 year old and weight for height for children older than 1 year old. Height for age will be calculated for all children.

#### Health system (secondary) outcomes

Healthcare consumption data will be extracted from the electronic health records, including: the length of hospital/JPH stay, the number of (pediatric intensive care unit) readmissions, emergency department visits and visits to the general practitioner (GP) or GP emergency services in the year following discharge.

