**Figure 2 F2:**
[figure not shown]
Simplified generic directed acyclic graph for hospital length of stay and parental stress.

A model will be created to predict treatment. Confounders identified with the DAG will be used as covariates to predict the probability of each patient being in the treatment group using a logistic regression (Bernoulli distribution), generating ‘propensity scores’. The regression model will be:

$$Treatment\;=\;\beta_{0}\;+\;\beta_{1}X^{T}+\varepsilon$$

where, $X^{T}$ is the matrix of confounders.

Samples of propensity scores will be generated: many propensity scores will be obtained from the posterior distribution.

Propensity scores will be converted into inverse probability of treatment weights using the formula:

$$\frac{\text{Treatment}}{\text{Propensity score}}+\frac{1-\text{Treatment}}{1-\text{Propensity score}}$$

An outcome model will be run using these weights: a Gaussian model will be used for numerical outcomes, and a cumulative probit model will be used for ordinal outcomes. The regression model used for the outcome analysis will be:

$$Outcome\;=\;\gamma_{0}\;+\;\gamma_{1}\times Treatment\;+\;\varepsilon$$

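### Death is not a listed outcome and 12-month healthcare use is a raw count without time at risk, so a shorter life would tend to lower the count and no listed outcome would show it

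*Protocol article*

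**What the plan says.** The Outcomes section of the protocol article states: "A full overview of outcomes including measurement tools and timing is presented in table 1". Death and survival are not in that table. The child-focused outcomes "will encompass the child’s quality of life, the parent-perceived health status of the child and growth". The descriptive variables under Additional analyses do not include death either.

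The healthcare-consumption row of Table 1 reads "Length of hospital/JPH stay, number of (PICU) readmissions, emergency department visits", followed by visits to the general practitioner, with timing "12 months of follow-up". The Health system (secondary) outcomes section repeats this as "the number of (pediatric intensive care unit) readmissions, emergency department visits" and general-practitioner visits in the year after discharge. Neither place gives a rate or a person-time denominator.

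The section on Bayesian inverse probability weighting says that "a Gaussian model will be used for numerical outcomes, and a cumulative probit model will be used for ordinal outcomes". The regression printed there contains an intercept, a treatment term and an error term, with no exposure time and nothing for death or censoring.

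On who is enrolled, the inclusion criteria admit children with complex chronic conditions or continuing technology dependence, including invasive ventilation through a tracheal cannula, provided the condition is stable and/or treatment is set. Children needing end-of-life care are excluded.

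**The concern.** The introduction hypothesises a favourable effect on healthcare consumption, and the intervention gradually hands care over to parents. A lower number of readmissions or emergency visits can be read as favourable only if one also knows that the children were alive to be readmitted. A count over a nominal year treats a child followed for two months and a child followed for twelve as equally observed.

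Some deaths are foreseeable in this population, even with the end-of-life exclusion. Unequal mortality is also conceivable on the authors' own account. Under Study limitations they say that the control children may need less intensive care, and that unmeasured confounding may remain after weighting.

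A second gap concerns the starting point. The follow-up year begins at discharge, and a stay in the transitional unit (JPH) lasts from one week to three months. A child who dies before discharge home has no follow-up year and no distress measurement at discharge home, so that death falls outside every listed post-discharge outcome.

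**Working it through.** **Inputs from the article.** About 50 JPH and 100 control children (Sample size); counts over 12 months (Table 1); outcome model with intercept and treatment only. The article gives no mortality rate, event rate or power calculation, so there is no figure of its own to reproduce on this point.

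**Assumptions.** Every mortality figure below is illustrative. Use runs at a constant rate r per year until death. The true rate is the same in both groups. Children who die live on average a fraction f of the year, with f from 1/12 (death at 1 month) to 0.5 (6 months). Events are counted up to death and the child stays in the analysis.

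**One child.** At r = 4 events a year and death at 1 month, the expected count is 4 × 1/12 = 0.33 instead of 4. To match a survivor's count, use before death would have to be 1/f times higher: 12 times for death at 1 month, 4 times at 3 months, 2 times at 6 months.

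**Group level.** With 12-month mortality m, the expected count per child is r × [1 − m(1 − f)]. The JPH/control ratio of mean counts is therefore [1 − m₁(1 − f)] / [1 − m₀(1 − f)].

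| Assumed mortality, JPH vs control | f = 1/12 | f = 0.5 |
|---|---|---|
| 5% vs 5% | 1.00 | 1.00 |
| 10% vs 5% | 0.908/0.954 = 0.95 | 0.950/0.975 = 0.97 |
| 15% vs 5% | 0.8625/0.954 = 0.90 | 0.925/0.975 = 0.95 |
| 5% vs 10% | 0.954/0.908 = 1.05 | 0.975/0.950 = 1.03 |
| 5% vs 20% | 0.954/0.817 = 1.17 | 0.975/0.900 = 1.08 |

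A Gaussian model estimates a difference in means, here −r(m₁ − m₀)(1 − f). At r = 4 and 10% vs 5%, that is −4 × 0.05 × 0.917 = −0.18 events per child (f = 1/12) or −4 × 0.05 × 0.5 = −0.10 (f = 0.5).

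**With time at risk.** Expected events divided by expected time alive equals r in both groups, so the rate ratio is 1.00 in every row.

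**Could deaths be compared formally?** At 10% vs 5% one expects 50 × 0.10 = 5 and 100 × 0.05 = 5 deaths. Two-sided power at 0.05 is Φ[(|d| − 1.96·SE₀)/SE₁], where SE₀ is the pooled and SE₁ the unpooled standard error.

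- Pooled proportion: 10/150 = 0.0667.
- SE₀ = √(0.0667 × 0.9333 × (1/50 + 1/100)) = 0.0432.
- SE₁ = √(0.09/50 + 0.0475/100) = 0.0477.
- Power = Φ[(0.05 − 0.0847)/0.0477] = Φ(−0.73), about 23%.

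The same formula gives about 15% for 5% vs 10% and 72% for 5% vs 20%.

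**The case against.** The strongest reply is that the article never says how a child who dies is handled. Such a child might be counted to death, set to missing or excluded. The worked analysis and code sit in supplemental file 7, which is not shown, and handling of deaths and offsets is often left to an analysis plan. This stands against the tempting reading that a dead child is scored as a low user: that is a consequence of the printed definitions, not a stated rule. It does not remove the point. Excluding such children or setting them to missing restricts the comparison to survivors, and the reader would still need deaths by group. Whether death is an outcome is also protocol content, and the article calls its list full.

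Other parts of the reply stand.

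- A reader might infer that a survival difference cannot be seen. Nothing prevents the investigators from reporting deaths; it is only that no listed outcome would show them.
- A reader might infer a bias favouring the JPH. It goes that way only if JPH deaths are more frequent or earlier, and reverses if controls die more. Intensive use before death could also raise a child's count.
- A reader might infer that questionnaires go to bereaved parents unchecked. The article gives completion windows and is silent on vital-status checks, a site procedure that an article normally omits.
- The requirement for a stable condition and/or set treatment, together with the end-of-life exclusion, limits the number of deaths.

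**Conclusion.** The point holds in a limited form. The outcome list, declared full, omits death, and the 12-month use outcomes are raw counts in a model without time at risk. Followed as written, a child who dies during follow-up would tend to lower the count, and no listed outcome would reveal a survival difference.

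The size is modest and conditional: about 3–10% on the mean count for an assumed mortality gap of 5 to 10 points with deaths at 1 to 6 months, in favour of the group with more deaths, and nil when mortality and its timing are equal. This rests on assumed mortality, a constant rate of use until death, and counting up to death. The documents support neither a particular direction nor a claim that bias is present.

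Parental distress at discharge home, the primary outcome, is unaffected by deaths after discharge. The count argument concerns one group of secondary outcomes. It merits correction mainly because healthcare use in this population is hard to interpret without survival beside it.

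**What to change.** 1. Extract date of death and date last known alive from the health records already being used.
2. Add all-cause death from enrolment to 12 months after discharge to Table 1 as a descriptive secondary outcome by group, including deaths before discharge home.
3. State how children who die enter the healthcare-use outcomes. Analyse readmissions, emergency visits and general-practitioner visits per time alive and followed, using a count model with a log time-at-risk offset under the same weighting, in place of a Gaussian model on raw counts. Read the rates together with the deaths.
4. Optionally add days alive and out of hospital over 12 months as a supporting measure, with days after death counted as zero. It should not be described as ranking death worst: a child at home for 10 months who then dies scores about 304 days, against 365 − 100 = 265 for a survivor with 100 hospital days.

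The cost is two extra date fields, one more descriptive outcome and a change of model for the counts, without patient contact. With about 50 and 100 children the comparison of deaths would be descriptive only and should be labelled so.

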### Recruitment

Parents will be recruited during hospitalisation in one of the participating UMCs and/or stay in the JPH. The study will be advertised to clinicians in relevant departments with a request to consider whether patients on the ward may be eligible. Screening of patients will be done weekly. The treating physician will ask eligible candidates for permission to be contacted by the researcher. The local researcher will then explain the study orally and in writing to the parents and provide a patient information letter. If interested, parents provide online informed consent. Children aged 12–18 must also provide their own online consent. For all patients, it is checked whether they are already enrolled in a standard follow-up programme to ensure that questionnaires are not duplicated. This is done only after obtaining informed consent from the participants.

### Data collection and management

On obtaining written informed consent, the researcher will assign a research subject ID number to patients. Every UMC has its own encryption key. Medical and healthcare consumption data will be extracted by the research team from the electronic health records and will be entered in a password-protected online database (Castor EDC). Parent reported data will be collected through online questionnaires using the KLIK PROM portal, which is an online portal to systematically monitor PROs in children with various chronic diseases and their parents over time.^48^

A KLIK research website is specifically created for the BRIDGE study, providing access to study information and allowing completion of questionnaires. The website is accessible only to the study team with a password (www.bridgetrial.nl). Parents receive a unique login token, allowing them to complete the questionnaires online, with the flexibility to take breaks as needed. The expected required time-investment of the parents to fill in the questionnaire is approximately 2.5 hours in total (around 50 min at three different time points).

The questionnaire completion windows are defined as follows:

On hospital discharge, participants are expected to fill out the questionnaire within the period of 48 hours before and 48 hours after discharge.At the 3-month follow-up, the window extends to 2 weeks before and 2 weeks after this point.At the 12-month follow-up, the window extends by 2 weeks before and 2 weeks after this point.

Parents will receive a one-time €20 gift card as a token of appreciation for their participation.

### Statistical analysis

Analysis of the primary and secondary outcomes will be done using Bayesian inverse probability weighting methods.^49^,^51^ All analyses will be performed using RStudio software (V.4.0.3). In online supplemental file 7 and an online blog, we demonstrate through data simulation how we will measure the effect, including the pertinent R code and rationale behind our methodological selection.

### Bayesian analysis

Bayesian analysis principles will be used to evaluate the effect of the JPH. This approach is adopted due to the constrained data points available in the BRIDGE study. Unlike traditional significance tests, which focus on determining whether an effect is statistically significant by testing how likely the observed data are conditional on the null hypothesis being true, our Bayesian analysis aims to estimate the probability that the intervention has a specific effect given the data. Bayesian methods are particularly beneficial for relatively small sample sizes, because they allow the incorporation of prior information and provide more intuitive and interpretable results.^49^ Additionally, Bayesian analysis can produce credible intervals that directly reflect the uncertainty about parameter estimates, making it a robust choice for our study with limited data.

